## Post-intervention evaluation of CHW Practice:

At the end of phase 1 (and repeated at the end of phase 2), an evaluation will examine the current practice of CHWs in diagnosis, treatment and referral of malaria cases. The objective is to describe differences in practice between the two arms of the trial.

Secondly the post-intervention study will use structured observational studies (using a checklist), semi-structured interviews with the CHWs, their community health supervisor (CHS) and others involved in CHW task scheduling, and review of programme records on the activities of CHWs who will be included in the study. This will provide information on current practices, standards, quality and deficiencies (Annex 1).

The study will establish indicators and potential explanatory variables through interviews, observation and review of programme records, with the primary comparison being between the two intervention arms:

Review of Programme Records:

- Number of CHW activities per month for each HP attached to our trial clinics over the trial length.
- Type of activity (proportion health education, preventative, consultations)
- Age range of patients seen by CHWs
- Location of activities (travel log) – primary data spanning 1 typical month
- Number of consultations per week with reasons for each (e.g. malaria, URTI, distribution of condoms, etc)
- CHW supervisory visits by CHSs and visits by CHWs to CHSs (frequency, what tools are used during these visits, feedback mechanisms) – previous month (May 2011 – AFG Calendar)

Data collected from a sub-group for more detailed interviews, stratified by province, gender and clinic type (CHC vs. BHC) (Soc Sci Officers).

- Current CHW practice where malaria is suspected, using case studies and in depth interview techniques – primary interview in random subsample.
- Motivation for the job
- Time per activity data – pre and during the trial (at end of phase 1) over 1 week
- Knowledge of malaria, fever, IMCI, and blood safety
- Current CHW IMCI practice using case studies and in depth interviews
- Current CHW referral practice (under what clinical circumstances and how many per week)CHW drug stock (types, quantity, expiry dates, storage conditions)
- CHW re-stock procedure (via interview if it does not occur during observation)
- CHW job-aids and reporting templates (types provided, how they are used)
- CHW basic training (description of what is covered) and any further training given

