### Trial Arms:

**Phase I:**

*Arm 1: Non-intervention arm:*

The non-intervention arm will be based on the existing clinical diagnosis, pre-referral treatment and referral to a clinic in areas where RDTs have not been deployed at CHW level. Arm 1 CHWs will receive refresher training according to the National Strategy for CBMM which includes the current IMCI guidelines.

Vs:

*Arm 2: RDT Arm*

Provision of community level diagnostics by rolling out RDTs to CHWs through the national strategy for Community based Management of Malaria. The arm has been designed exactly as the current National guidelines for RDT implementation..The arm will include:

- Clinic level microscopy or RDT and CHWs using RDTs to provide parasitological diagnosis to diagnose, treat and/or refer patients. Under this scheme, CHWs will be provided with CQ, SP and artesunate (AS). Depending on the diagnostic result, they prescribe according to the National Treatment Guidelines (CQ for confirmed vivax, SP and AS for confirmed falciparum, and no antimalarial for a negative result).
- CHW training will be conducted exactly as described in the CBMM strategy, using a “trickle down approach” where Training of Trainers takes place at the central level for provincial trainers of local NGOS who run the health service. These, in turn, run workshops for training CHSs and CHWs (see section 2.2 for pre-evaluation of training and roll-out). Participants will receive training to enforce revised IMCI guidelines, taken from the CBMM strategy document, which include an RDT in the algorithm for fever (see annex 2).
- There are no plans for additional support or refresher training, and no plans for quality control and assurance contained in the National Plan.
- CHWs are not equipped with suitable storage facilities for the RDTs, for example evaporative coolers.
- Monitoring and evaluation takes place according to the draft strategy.

The second phase of the trial will be initiated in Feb 2012. The second phase of the trial will re-randomise clinics to either the RDT arm (as in arm 2, above) and a third arm (arm 3). The third arm will answer the question: “how can the performance of RDTs at community level be enhanced?”. The same set of outcomes will be used to measure the relative effectiveness of each approach. A revised random allocation using the same methods will be conducted for the Phase II randomisation.

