### Results of randomisation

The final choice of restriction criteria resulted in 1598 acceptable allocations from which one was randomly chosen. Table 2 and **Error! Reference source not found.** summarise the allocation process.

6 clinics (clusters) have been allocated to each study arm in the Nangahar stratum, and 5 per arm in Kunduz stratum. Study arm 0 denotes no RDT, and study arm 1 denotes RDT (intervention) – see next section.

Table 2: Results of intervention allocation process

| **Kunduz** | | |  | **Nangahar** | | |
| --- | --- | --- | --- | --- | --- | --- |
| **Cluster** | **Clinic** | **Study arm** |  | **Cluster** | **Clinic** | **Study arm** |
| 1 | Ajighan | 0 |  | 11 | Baro | 0 |
| 2 | AngorBagh | 0 |  | 12 | Batikot | 1 |
| 3 | ArbabRamazani | 0 |  | 13 | Behsood | 0 |
| 4 | BolaQachi | 1 |  | 14 | Chardhi | 1 |
| 5 | CharSari | 1 |  | 15 | GardiGhos | 1 |
| 6 | Khan Abad | 1 |  | 16 | Khewa | 0 |
| 7 | KhwajaGhaltan | 0 |  | 17 | LandaBuch | 0 |
| 8 | Madrasa | 1 |  | 18 | MamandDara | 1 |
| 9 | Nick Pay | 1 |  | 19 | NajmulQura | 1 |
| 10 | SandoqSai | 0 |  | 20 | Rodat | 0 |
|  |  |  |  | 21 | SangarSarai | 1 |
|  |  |  |  | 22 | Shegay | 0 |

Table 3: Summary of clusters allocated to study arms in Phase 1

| **Arm 0 (no RDT)** | **Arm 2 (RDT)** |
| --- | --- |
| Ajighan | Batikot |
| AngorBagh | BolaQachi |
| ArbabRamazani | Chardhi |
| Baro | CharSari |
| Behsood | GardiGhos |
| Khewa | Khan Abad |
| KhwajaGhaltan | Madrasa |
| LandaBuch | MamandDara |
| Rodat | NajmulQura |
| SandoqSai | Nick Pay |
| Shegay | SangarSarai |

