**Figure 2: Phase 2 trial schematic.**

### Case definition and patient enrolment:

Patients will be drawn from the communities where the CHWs operate and the clinics which supervise and support those CHWs. Inclusion criteria will be:

- Any patient where the CHW* or clinician considers malaria in the diagnosis – either prescribing an antimalarial or would request a malaria test if available or referring for diagnosis of malaria elsewhere.
- Patient, or parent/guardian, gives informed consent to the study.

*any community health worker who consults with patients and prescribes treatment, and is administratively attached to one of the study clinics.

Exclusion criteria will be

- Patients with a diagnostic result from another facility.
- Patients referred on for diagnosis in the private sector.
- Patients who have signs of severe or complicated disease and are referred prior to giving any diagnosis using the interventions.

Patients can be enrolled during any consultation with a CHW no matter where it takes place. The consultation could be made at the health post, the patient’s residence, or even outside in the street or fields. The CHW will also use the standard national HMIS tool for recording all their consultations, which will also allow assessment of any changes to practice within the community by identifying changes in the number of each type of consultation (for example, community DOTS, health awareness, condom distribution, etc).

If the patient gives informed consent, the CHW will assign a unique patient number and note the patients information on a pro-forma pictorial record form (Patient Tracking Form, see section 2.6). The patient tracking form has been designed for semi literate and illiterate health workers and has been pretested and validation in field testing using CHWs in Nangahar province.

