### Sample Collection:

Filter paper blood spots will be collected from participants. These will be collected using clean disposable lancets and gloves at the same time as the RDT is used. If the RDT is not used (i.e. in the non-intervention group) then the filter paper will be collected during the consultation. Filter papers will be stored in ziplock bags with silica beads. They will be returned to the clinic within 7 days and stored in a refrigerator (4^o^C) until shipped to Kabul for evaluation (see 2.8.4, below)

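### The severe-disease exclusion depends on an undefined, post-allocation act that differs between Phase I arms, so the same referred patient can be excluded in Arm 1 and kept in Arm 2

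*Protocol*

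**What the plan says.** In the Protocol, Case definition and patient enrolment, the inclusion rule is broad. It admits any patient in whom the CHW or clinician considers malaria, "either prescribing an antimalarial or would request a malaria test if available or referring for diagnosis of malaria elsewhere". A patient who is only being referred for malaria diagnosis can therefore qualify. The third exclusion criterion then removes "Patients who have signs of severe or complicated disease and are referred prior to giving any diagnosis using the interventions". Two conditions must both hold: severe signs, and referral before a diagnosis of the stated kind.

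Under Trial Arms (Phase I), Arm 1 is named the non-intervention arm and works by "existing clinical diagnosis, pre-referral treatment and referral to a clinic". Arm 2 has "CHWs using RDTs to provide parasitological diagnosis to diagnose, treat and/or refer patients". Results of randomisation ties the word to the test: "Study arm 0 denotes no RDT, and study arm 1 denotes RDT (intervention". Sample Collection does the same: "If the RDT is not used (i.e. in the non-intervention group) then the filter paper will be collected during the consultation".

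Elsewhere the word is used more loosely. Post-intervention evaluation of CHW Practice describes its analysis "with the primary comparison being between the two intervention arms", and Randomisation Methods also speaks of allocating clusters to two intervention groups. The enrolment section does not say which usage applies to the exclusion.

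**The concern.** Eligibility in a cluster trial should rest on what is true of the patient before the arm can influence it. Here clinics are allocated first. Patients are then enrolled by CHWs who know whether they hold RDTs, and whether a severe patient is kept depends on what the CHW does during the consultation, and in what order. The act that keeps the patient in is not the same, or not available, in both arms.

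Randomising clinics does not protect against this. The arms may end up with different mixes of severe, referred patients, who could plausibly differ from the rest in malaria status, drugs given and referral. The Statistical Methods section lists symptom severity as an explanatory variable, so the protocol itself treats it as relevant. Adjustment cannot recover patients who were never enrolled.

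Referral outcomes also depend on enrolment. The clinic-level text describes patients who did not visit a CHW and patients already enrolled by one. A patient who saw a CHW, was excluded and was then referred fits neither description.

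**Working it through.** **Step 1: apply the criterion to a patient with severe signs seen by a CHW in Phase I.** Reading A takes the interventions to mean the RDT. Reading B takes them to mean each arm's own diagnostic method.

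| What the CHW does | Arm 1 | Arm 2 |
| --- | --- | --- |
| Refers at once, no diagnosis | Excluded (A and B) | Excluded (A and B) |
| Diagnoses clinically, no RDT, then refers | Excluded (A); kept (B) | Excluded (A and B) |
| Does an RDT, then refers | Does not arise | Kept (A and B) |
| Treats and does not refer | Kept (A and B) | Kept (A and B) |

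On Reading A, all severe referrals by Arm 1 CHWs are excluded, while those in Arm 2 are excluded or kept according to whether the RDT came first. On Reading B, a clinical diagnosis keeps the patient in Arm 1 but only an RDT does so in Arm 2. Neither reading gives one rule for both arms.

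**Step 2: possible size for the primary outcome, on Reading A.** The plan has no figure for this, so there is nothing to reproduce.

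- From the documents: planned correct treatment of 10% in Arm 1 and 50% in Arm 2, a difference of 40 points (Sample Size Assumptions); 1262 patients planned in the RDT arm (Table 4).
- Assumed: s, the share of Arm 2 patients who are severe, tested and then referred, 1% to 5%; r, the proportion of them correctly treated, 0 to 100%.
- Formula: Arm 2 rate = (1 − s) × 0.50 + s × r.

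| s | Patients (s × 1262) | Arm 2 rate, r = 0 to 1 | Difference from 10% |
| --- | --- | --- | --- |
| 1% | about 13 | 49.5% to 50.5% | 39.5 to 40.5 points |
| 2% | about 25 | 49.0% to 51.0% | 39.0 to 41.0 points |
| 5% | about 63 | 47.5% to 52.5% | 37.5 to 42.5 points |

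Worked for s = 5%: 0.95 × 0.50 = 0.475 with r = 0; 0.475 + 0.05 = 0.525 with r = 1.

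**Step 3: the same for a secondary outcome.** Antibiotic use in malaria-negative patients is planned at 5% in Arm 1 and 15% in Arm 2, a contrast of 10 points. Suppose 5% of the Arm 2 negatives are such severe patients and 0 to 100% of them receive an antibiotic. The Arm 2 rate becomes 0.95 × 0.15 = 14.25% at the low end and 14.25% + 5% = 19.25% at the high end. The shift is −0.75 to +4.25 points. At a 1% share the range is 0.99 × 0.15 = 14.85% to 15.85%, a shift of −0.15 to +0.85 points.

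**The case against.** The best defence is that the criterion does not mention the RDT and that the protocol often uses the word intervention for both arms. A sensible reader could take it to mean referral before the arm's own diagnosis. This stands as far as it goes: it would be too strong to say without qualification that the excluding condition is always met by Arm 1 referrals. It does not remove the problem, because Step 1 shows the cut-off is then a clinical diagnosis in one arm and an RDT in the other. Sites could also apply either reading.

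It is also fair that the route may be rare. The fever algorithm taught to Arm 2 CHWs is in Annex 2, whose figure is not available here. If it places referral for severe signs before testing, few Arm 2 patients would be tested first.

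Three stronger readings are tempting but not supported:

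- A reader might infer that Arm 1 can contain no severe patients. The criterion also requires referral, so severe patients who are treated and not referred stay eligible in both arms.
- A reader might infer that severe cases would dominate the small Arm 2 falciparum group. The documents give neither the frequency of severe disease nor the falciparum rate among severe patients, so no share can be stated. The Sample size section already treats the falciparum analysis as exploratory.
- A reader might infer the same fault in Phase II because Arm 3 training could change the order of testing and referral. Both Phase II arms use RDTs, and nothing in the documents shows that the order would differ.

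**Conclusion.** The point holds as a fault in the eligibility rule. The exclusion turns on an undefined act that happens after allocation and is not the same in both Phase I arms. On the protocol's main labels it removes all severe patients referred by Arm 1 CHWs and only some of their Arm 2 counterparts.

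The effect on the primary outcome is probably small: at most 2.5 points either way at an assumed 5% share, against a planned 40. It does not threaten the main Phase I conclusion if the planned difference is near the truth. Antibiotic use, with a planned contrast of 10 points, could be affected more in relative terms, as could referral outcomes. The direction is unknown, and all these sizes rest on assumed shares and on extreme outcome rates among the affected patients. The case for changing the text is that the asymmetry is avoidable, later adjustment cannot repair it, and the change is cheap.

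**What to change.** Replace the third exclusion criterion with one based only on signs of severe or complicated illness at presentation, assessed before any test or treatment. Word it identically for all arms and state that it applies whether or not an RDT is done afterwards. Add a tick box to the screening record so that patients excluded for this reason can be counted and reported by arm.

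This changes who is eligible for analysis only. How such patients are managed stays as the arm and national guidance already provide.

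The cost is one sentence and one tick box. A few tested severe patients leave the RDT-arm datasets, and severe patients who are not referred, now eligible everywhere, would leave all arms. CHWs who know their arm, and whose training differs by arm, would still judge severity. The change therefore reduces the dependence on arm but does not abolish it, which is why the counts by arm are needed.

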## Outcomes:

The trial outcomes are presented below. In addition, the RDT arm (arm 2) will be subjected to an interim evaluation for which outcomes are also presented.

### Trial Primary Outcome:

The primary outcome of the study is:

- Proportion of patients (in)correctly treated by CHWs.

Correct treatment is defined as:

- - Treatment of PCR confirmed Pf with SP/AS.
  - Treatment of PCR confirmed Pv with CQ (regardless of accompaniment with SP or addition of primaquine).
  - No antimalarial for PCR confirmed negative diagnosis.

### Trial Secondary Outcomes:

- % of Pf cases treated with ACT.
- % of patients <10 years of age who are correctly treated (estimated at 40% of all patients)
- % of malaria negative patients receiving antimalarial drug
- % of malaria negative patients receiving antibiotics
- % of patients treated per policy

Per policy defined as:

- Suspected malaria which is PCR confirmed treated with CQ/SP
- Community based diagnosed Pf, subsequently confirmed as Pf treated with SP/AS
- Community based diagnosed Pv, subsequently confirmed as Pv treated with CQ
- No antimalarial given to negative cases (confirmed by PCR)
- Proportion of patients incorrectly treated in each arm, including data collected at the clinic level.
- Time to first treatment from onset of symptoms.
- Cost per patient correctly treated.
- Cost per patient treated per policy.
- Invalid rate, specificity and sensitivity of RDTs deployed at community level (against PCR).
- Number of patients attended by CHWs and type of attendance.
- Number and proportion of patients successfully referred by CHWs to BHCs.
- Proportion of malaria negative and positive given antibiotics at CHW and/or clinic level.

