While the rollout of RDTs at clinic level has some evidence base (in part, from the previous ACTc studies), there is little available data on the effectiveness with which this intervention can be provided at community level through CHWs. The data that does exist locally is based on two studies, one conducted in 2006^[[1]](#footnote-1)^ and one ongoing pilot programme^[[2]](#footnote-2)^. Evidence from the study and from the pilot programme suggests that RDTs are not utilised effectively by CHWs. In the study, high rates of invalid tests were reported due to user error, and in both programmes, RDTs are incorrectly applied to patient’s symptoms. The results are that very large numbers of RDTs are used, and very few cases of malaria are adequately detected. The effect of RDTs on treatment decisions and accuracy was not noted by either study.

Use of RDTs at community level will also have an effect on current guidelines for management of febrile illness and diseases of children. The current community IMCI guidelines for Afghanistan (and most of Asia) do not include RDTs in the differential diagnosis of childhood diseases in the community. The current guidelines favour a blanket approach to treatment of “suspected malaria” where there is no other obvious cause of illness and the patient is in an endemic area. Changing these guidelines requires an evidence based approach to assess both the clinical and economic aspects of the intervention – something which has thus far not been conducted despite the trend in programming which has now started to deploy RDTs much more widely.

This study aims to provide evidence on the effectiveness of RDTs that have been deployed at community level by measuring the accuracy of the tests themselves, and the accuracy with which treatment is provided to malaria positive and malaria negative cases.

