## Outcome Measurement and Recording:

### Outcome Measurement:

In the community healthcare setting, there are several possible outcomes to any consultation with a CHW. Once the initial consultation is made, the CHW will decide on a diagnosis and then a specific course of action. In addition, patients may present at the clinic, either after a consultation with a CHW, or without a consultation. In the former case, the patient may have been referred, or may have self referred. The patient may also attend the clinic without having a consultation with a CHW (figure 3).

**Figure 3: Schematic diagram showing the potential path of a patient through the health system, starting at community level,**

Data and outcomes will be recorded at both the clinic and community level. The outcomes will be measured against PCR based diagnosis of malaria (including Pf, Pv, *P ovale* and *P malariae*). Filter paper blood spots will be collected at the diagnosis stage (at community and clinic level).

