### Risks and potential adverse events:

There are minimal risks associated with this study. Blood samples would, in most cases, be taken anyway for the application of the RDT is associated with minimal risk of secondary infection at the puncture site and with mild pain.

The main risk is in the mistreatment of falciparum malaria with either no antimalarial or with an ineffective antimalarial (i.e. CQ). Currently, falciparum malaria is quite rare in the study areas (although it may vary seasonally and geographically) so the risk of this occurrence is low. According to the National Guidelines and the study protocol, all Pf positive patients will be referred to a clinic for further evaluation which further reduces the risk of this occurring, since all clinics will have parasitological diagnosis available (either through RDT or through microscopy).

The trial intervention arm is unlikely to increase this risk, in fact, rather the opposite. This potential adverse event will be monitored throughout the trial and its occurrence will be reported to the Data Safety and Monitoring Board (DSMB). Immediately following a PCR result which is positive for Pf (regardless of coinfection), results from the patient record form will be cross checked to see which treatment was given. Because of logistical constraints, PCR results will not be known for more than 2 weeks after the initial assessment of the patient. Every effort will be made to trace the patient and ensure that they have recovered. If not, they will be referred to the health facility for further treatment.

Depending on the frequency with which this event occurs, the study staff will inform the DSMB of any action being taken which could include re-training of staff or withdrawal of CHWs from the trial. All efforts will be made to follow-up the patient within a few days of knowing the PCR result. All patients will be advised by CHWs to seek treatment at the clinic if symptoms recur or continue following the treatment.

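### The per-policy treatment outcome is scored against PCR, which is unavailable when treatment is chosen, so policy-following treatment can be counted as off-policy, most of all in arm 1

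*Protocol*

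**What the plan says.** Section 2.6.2 lists the percentage of patients treated per policy as a secondary outcome and gives four qualifying lines:

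- The first concerns clinical suspicion: "Suspected malaria which is PCR confirmed treated with CQ/SP".
- The second concerns falciparum and asks for agreement between the community result and the later one: "Community based diagnosed Pf, subsequently confirmed as Pf treated with SP/AS".
- The third is the vivax counterpart and is built in the same way: "Community based diagnosed Pv, subsequently confirmed as Pv treated with CQ".
- The fourth covers negative patients from whom antimalarials are withheld, with negative status again set by PCR.

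The same section lists a cost per patient treated per policy. Section 2.7.1 sets the general reference: "The outcomes will be measured against PCR based diagnosis of malaria". Section 2.10.3 gives the timing: "PCR results will not be known for more than 2 weeks after the initial assessment of the patient".

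The policies themselves are described elsewhere. For suspected malaria without RDTs, section 1.2 says: "The current guidelines favour a blanket approach to treatment of" such cases, on condition that no other cause is obvious and the area is endemic. Section 2.5.1 gives arm 1 clinical diagnosis, pre-referral treatment and referral, with training in the current IMCI guidelines. For arm 2 it says of the CHWs: "Depending on the diagnostic result, they prescribe according to the National Treatment Guidelines". The arm 3 description repeats this.

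**The concern.** A measure of treatment according to policy should ask whether the CHW did what the policy directs, given what the CHW knew. Neither policy uses PCR, and neither could, because the result comes weeks later. The definition nevertheless makes a PCR result a condition of every line.

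Two kinds of policy-following treatment then fail. In arm 1, a suspected case treated under the guideline fails if PCR is negative. In arms 2 and 3, a patient treated by the RDT result fails if PCR disagrees. The first is likely to be much more common than the second, because section 1.2 describes vivax as a minority cause of febrile illness and section 2.9.1 puts RDT accuracy above 95%. The misclassification therefore differs between arms and favours the RDT arm. A difference in this outcome could be reported as better adherence when it reflects only the difference between the two policies. The cost ratio carries the same error in its denominator.

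**Working it through.** The protocol gives no expected rate, sample size or power for this outcome, so there is no planned figure to reproduce. The check scores arms that follow policy in every case, under the section 2.6.2 definition.

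**Inputs**
- *p*, PCR positivity among enrolled patients: not given. Assumed 5–30%.
- *t*, share of arm 1 patients given CQ/SP, the rest receiving no antimalarial: not given. Shown at 1, 0.9 and 0.5, and assumed independent of PCR status. For orientation, section 2.8.1 plans for 90% of malaria-negative arm 1 patients receiving an antimalarial.
- RDT agreement with PCR: assumed 95%. Section 2.9.1 reports accuracy above 95% but does not name the reference standard or separate sensitivity from specificity.

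**Arm 1.** A treated patient counts only if PCR-positive, and an untreated patient only if PCR-negative:

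score = p·t + (1 − p)(1 − t)

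**Arm 2.** Treatment always follows the RDT, species errors ignored:

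score = p × sensitivity + (1 − p) × specificity = 0.95 for any p when both are 95%.

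**Results**

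| t | p | Arm 1 score | Gap to 95% |
|---|---|---|---|
| 1 | 0.05 | 0.05 + 0 = 5% | 90 points |
| 1 | 0.30 | 0.30 + 0 = 30% | 65 points |
| 0.9 | 0.05 | 0.045 + 0.095 = 14% | 81 points |
| 0.9 | 0.30 | 0.27 + 0.07 = 34% | 61 points |
| 0.5 | any | 0.5p + 0.5(1 − p) = 50% | 45 points |

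True adherence is 100% in both arms in every row, provided that the untreated arm 1 patients were also managed as policy allows, for example by referral. The gap comes from the definition alone.

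**Sensitivity to RDT performance.** With an assumed sensitivity of 75% and specificity of 95%, arm 2 scores 0.05 × 0.75 + 0.95 × 0.95 = 94% at p = 0.05 and 0.30 × 0.75 + 0.70 × 0.95 = 89% at p = 0.30. The gap narrows by 1 to 6 points.

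**Direction.** The arm 1 score changes with t at rate 2p − 1, which is negative whenever p is below 50%. Over the assumed range, the more suspected cases an arm 1 CHW treats, the lower the per-policy score.

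**Cost ratio.** Dividing by a denominator that is too small inflates the cost per patient treated per policy. At t = 0.9 the inflation in arm 1 is 1/0.14 = 7.1-fold at p = 0.05 and 1/0.34 = 2.9-fold at p = 0.30. In arm 2 it is 1/0.95 = 1.05-fold.

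**Overlap with the primary outcome.** Under sections 2.6.1 and 2.6.2 a PCR-negative patient is scored by the same rule: success if no antimalarial was given. At p of 5–30% that covers 95–70% of patients. Among PCR-positives the main difference is that the per-policy outcome credits CQ/SP for PCR-confirmed suspected malaria.

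**The case against.** The strongest reply is that section 2.7.1 commits the trial to PCR as the reference for its outcomes, so a PCR-based composite was a deliberate choice. That explains the wording. It does not turn a PCR-scored quantity into a measure of adherence to policies that do not use PCR.

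Four stronger readings are tempting, and the document does not support them.

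- *The gap is 65–90 points.* This needs every enrolled arm 1 patient to be treated. Section 2.5.1 includes referral, the inclusion criteria in section 2.5.7 admit patients who are only referred or for whom a test would be requested, and section 1.2 places conditions on the blanket approach. An arm 1 patient referred without an antimalarial and PCR-negative passes the definition. The size therefore depends on t.
- *The outcome fails in its purpose of separating adherence from test accuracy or from the policy itself.* The protocol states no such purpose. Parts of that question are also covered elsewhere: RDT sensitivity and specificity (section 2.6.2), a second reading of RDTs (section 2.9.3), and Annex 3 indicators 12 and 14 on RDT-confirmed cases. These do not cover arm 1, however, and the investigators' notes in Annex 3 change the denominators to suspected and PCR-confirmed cases.
- *The definition ignores arm, so an untested arm 2 patient given CQ/SP counts if PCR-positive.* That is the most literal reading of the first line. Its wording echoes the no-RDT guideline, and the Pf and Pv lines presuppose a species diagnosis, so a split by arm can be inferred. It should still be stated.
- *The outcome simply repeats the primary one.* It does not: PCR-confirmed Pf given CQ/SP is per policy under the first line but not correct treatment under section 2.6.1. Such cases should be few, since section 1.2 puts falciparum at around 5–10% of malaria cases.

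A late Pf result may also reach the CHW through patient tracing (section 2.10.3), so it would be too strong to say that CHWs never see PCR. What matters is that it is absent when treatment is chosen.

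**Conclusion.** The point holds. As written, the per-policy outcome counts policy-following treatment of PCR-negative suspected cases in arm 1, and RDT-following treatment that PCR contradicts in arms 2 and 3, as off-policy. It comes close to the primary outcome, and it biases both the arm comparison and the cost ratio.

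The direction is firm if most arm 1 patients are treated and positivity is below 50%. The size is not fixed by the document: about 65–90 points at t = 1, 61–81 at t = 0.9 and 45 at t = 0.5. These figures rest on an assumed p of 5–30%, treatment independent of PCR status in arm 1, and 95% RDT–PCR agreement.

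The primary outcome and the sample size are unaffected. PCR remains a suitable reference for correct treatment. The correction should be made, but it concerns one secondary outcome and the cost measure built on it. No view is taken on which treatment is right.

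**What to change.** Reconcile the per-policy definition in section 2.6.2 with the policies described in sections 1.2 and 2.5.1, using the information recorded at the consultation:

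- **Arm 1:** score treatment or referral against the recorded clinical diagnosis, under the guideline in force.
- **Arms 2 and 3:** score treatment against the RDT result the CHW recorded.
- State which line applies to which arm.
- Keep PCR for the correctly treated outcome.
- Compute the cost per patient treated per policy on the same basis.

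A fully adherent CHW then scores 100% in every arm, whatever the prevalence or RDT accuracy. If a PCR-based composite was intended, keep it under another name so that it is not reported as policy adherence.

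The cost is small. Section 2.7.2 says the CHW form already records the diagnosis, whether an RDT was used, its result and the action taken, so no new data are needed. The one piece of work is to write the scoring rule against the Annex 2 algorithm and a dated version of the national strategy, which section 2.6.3 describes as still in draft.
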